## Abstract

**Background:**

Thanks to advancements in medical care, a majority of patients with sickle cell disease (SCD) worldwide live beyond 18 years of age, and therefore, patients initially followed in paediatric departments are then transferred to adult departments. This paediatric-adult care transition is a period with an increased risk of discontinuity of care and subsequent morbidity and mortality. During this period, the patient will have to manage new interlocutors and places of care, and personal issues related to the period of adolescence. To take into consideration all these aspects, an interesting approach is to use the whole system approach to the patient, as presented in the biopsychosocial approach. The aim of this trial is to evaluate the impact of the proposed biopsychosocial paediatric-adult transition programme.

**Methods:**

The DREPADO study is a multicentre randomised control trial comparing a control group (Arm A) to an interventional group with a paediatric-adult transition programme based on a biopsychosocial approach (Arm B). To be included, patients should have the SS, SC, or Sβ form of sickle cell disease and be aged between 16 and 17 years. The randomisation in a 1:1 ratio assigns to Arm A or B. The primary outcome is the number of hospital admissions and emergencies for complications in the index hospital, in the 2 years after the first consultation in the adult department of care. Secondary outcomes consider the quality of life, but also include coping skills such as sense of self-efficacy and disease knowledge. To provide patient and parent knowledge and coping skills, the transition programme is composed of three axes: educational, psychological, and social, conducted individually and in groups.

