## Background

Sickle cell disease (SCD) is a chronic, genetic disease, widespread both around the world and in France. After diagnosis, patients with SCD require medical follow-ups, which are essential to prevent complications. The most frequent complications are vaso-occlusive crises (VOC; which are painful), acute chest syndrome (ACS), and stroke. Thanks to advancements in medical care, a majority of SCD patients worldwide live beyond 18 years of age [1], and therefore, patients initially followed in paediatric departments are then transferred to adult departments.

For patients with chronic disease such as SCD, this paediatric-adult care transition is a period with an increased risk of discontinuity of care [2, 3]. During this period, adherence to medication is sub-optimal [1, 4] and the rate of missed clinical appointments is high [5]. Furthermore, the highest morbidity and mortality is observed between 17 and 18 years of age [6], and young adults frequently use acute care (emergency care and hospitalisations) after paediatric-adult transition [7].

During the paediatric-adult transition, the patient will have to manage new interlocutors and places of care, as well as a different organisation of this. An important aspect to improve the health status of patients is, therefore, to involve both paediatric and adult departments of care in the transition [3]. In addition, the patient will have to manage personal issues related to the period of adolescence [8]: a period of psychological upheaval and adaptation of family roles [9]. To assess the needs of patients with SCD during this transition period, a qualitative study was conducted in Lyon (France). Parents, as well as adolescent and adult patients with SCD, were individually interviewed about it. Results revealed individual and also family needs that concerned knowledge of the disease, coping skills, therapeutics, and psychosocial aspects [10].

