## Methods/Design

### The aim, design, and setting of the study

The DREPADO RCT seeks to assess the impact of a paediatric-adult transition programme. This trial is an interventional study. It is an open-label, individual, multicentre RCT comparing a control group (Arm A) to an interventional group with a paediatric-adult transition SCD programme based on the biopsychosocial approach (Arm B).

The DREPADO trial is a French national RCT including centres specialised in SCD patient care, involved in the SCD health network (*Maladie Chronique du Globule Rouge et des autres maladies de l’érythropoïèse* Filière - MCGRE) accredited by the French Ministry of Health and motivated to participate in this study. The coordinating centre is Lyon University Hospital, and five other centres will participate (Créteil, APHP Kremlin-Bicêtre, Martinique, APHP Necker, Pontoise).

The follow-up period is a maximum of 4 years for each patient. Outcomes is assessed at baseline (T-inclusion), at transfer date – which corresponds to the first consultation in the adult department of care (T-transfer), 12 months after transfer (T-12), and 24 months after transfer (T-24).

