#### Inclusion criteria

Patients are included if they fulfil the following conditions: having the SS, SC, or Sβ form of SCD; aged between 16 and 17 years; orally agreeing to participate. The caregiver is included if they fulfil the following conditions: parent or legal guardian of the patient; aged more than 18 years; having provided a signed written consent for him/herself and for the patient.

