### Outcome measurements

The primary outcome is number of hospital admissions and emergencies in the index hospital for complications (i.e*.* VOC, ACS, and/or stroke) in the 2 years after T-transfer.

To evaluate the biopsychosocial approach, the secondary outcomes include bioclinical, psychological, and social factors, measured at T-inclusion, T-transfer, T-12, and/or T-24, collected from patients and/or parents. With regard to the indirect bioclinical factors, the use of care is evaluated by the incidence of emergency visits and medical consultations at T-24. Medication adherence is also measured at T-inclusion, T-transfer date, T-12, and T-24 by adapted Medication Intake Survey-Asthma (MIS-A) [17] adapted for SCD and Medication Adherence Report Scale (MARS) [18]. Psychological factors, such as pain perception, and social factors, such as school absenteeism is measured by self-declaration. Quality of life is evaluated using the brief World Health Organisation Quality of Life questionnaire (WHOQOL-Brief), and skills are measured by questionnaires, such as the health literacy using the European Health Literacy Questionnaire (HLS-EU-Q16) [19], self-efficacy feeling using the Self Efficacy Specific Instrument – Sickle Cell Disease (SCD-SES) [20]; these are measured at the T-inclusion, T-transfer, T-12, and T-24. All the data sources are presented in Table 2.

**Table 2 Tab2:** Data collection plan

Outcomes		Time point				Population		Data sources
		T-inclusion	T-transfer	T-12	T-24	Patient	Parent	
Use of care	Hospitalisations for VOC, ACS, stroke		X		X	X		Medical records
	Emergency visits, medical consultations, imaging exams		X		X	X		Medical records
Medication adherence		X	X	X	X	X		2 questionnaires (MARS and adapted-MIS-A)
School absenteeism			X		X	X	X	Auto declaration
Quality of life		X	X		X	X		26-item questionnaire (WHOQOL-Brief)
Health literacy		X	X		X	X		16-item questionnaire (HLS-EU-Q16)
Disease and therapeutic knowledge		X	X		X	X	X	36-item questionnaire
Patient activation		X	X		X	X		13-item questionnaire
Sense of self-efficacy						X		9-item questionnaire (SCD-SES)
Transition preparation		X	X		X	X		20-item questionnaire (TRAQ)
Pain perceptions	At home			X	X	X		Auto declaration (book)
	Intensity during hospitalisations		X		X	X		Medical records

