### Statistical analysis plan

Demographics and other characteristics are reported descriptively and according to treatment group. Means and standard deviation (SD), or medians and ranges when appropriate are calculated for continuous variables. Categorical variables will be presented using numbers and percentages.

The crude rate of hospitalisations due to complications will be calculated by dividing the total number of hospitalisations due to VOC, ACS, and stroke occurring after transfer by the total duration of follow-up of all patients in each group. The treatment effect will be assessed using a multivariable Poisson regression model with the study group as a factor, adjusting for minimisation factors and relevant patient characteristics and the length of follow-up as the offset. Results will be expressed as a rate ratio with 95% confidence interval. A negative binomial model will be fitted if data are over-dispersed. The same analyses will be performed for the association between intervention and other secondary outcomes.

Analysis of covariance (ANCOVA) will be used to evaluate the intervention effect at T-24 on all the secondary outcomes evaluated by questionnaires. Scores will be computed and depicted at each assessment by following the scoring procedures for each questionnaire. Each ANCOVA will include the baseline measure (T-inclusion) and minimisation factors as covariates. Changes over time for each score will be also assessed using generalized estimation equation analyses to test the effect of group, time, and the interaction group time after controlling for minimisation factors and relevant patient characteristics.

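### The primary window opens at the first adult consultation, an event after randomisation, so patients who never attend drop out of the primary comparison and the analysed arms are no longer protected by randomisation

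*Protocol article*

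**What the plan says.** All references are to the protocol article.

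- **Inclusion criteria:** patients enter while "aged between 16 and 17 years; orally agreeing to participate", and are randomised 1:1 by minimisation.
- **Outcome measurements:** "The primary outcome is number of hospital admissions and emergencies in the index hospital for complications", over the 2 years after T-transfer. The Abstract gives the same window as "in the 2 years after the first consultation in the adult department of care".
- **The aim, design, and setting of the study:** outcomes are assessed, among other points, "at transfer date – which corresponds to the first consultation in the adult department of care (T-transfer"). T-transfer is therefore an attended visit, not an age or a time since randomisation. The same section adds: "The follow-up period is a maximum of 4 years for each patient".
- **Statistical analysis plan:** the crude rate divides hospitalisations "occurring after transfer by the total duration of follow-up of all patients in each group". The model is Poisson, or negative binomial if over-dispersed, with length of follow-up as offset.
- **Discussion:** the programme starts in the paediatric department and continues in the adult one, so it is already running before the window opens.
- **Outcome measurements, Table 2:** "Hospitalisations for VOC, ACS, stroke" and emergency visits are taken from medical records at T-transfer and T-24.

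No start date is given for a patient who has no adult consultation.

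**The concern.** Randomisation makes the arms comparable on the day of allocation. The primary outcome is measured from a later day, which each patient reaches only by attending adult care. A patient who does not attend contributes neither events nor person-time. Attending late moves the window to an older age.

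Both whether and when the window opens could depend on the arm. The article justifies the programme by discontinuity of care and a high rate of missed appointments at transition, and one of its three axes concerns the patient's relationship to care. An effect on engagement with adult care is therefore plausible. If it occurs, the two analysed groups are selected differently, and adjustment for the minimisation factors need not undo that. The design effect is only a 15% reduction, so a modest selection effect could hide it or imitate it. The patients whose transition failed altogether would not be counted.

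**Working it through.** **1. The plan's own figure.** Inputs from Sample size and recruitment: control rate 3.5 per patient-year, rate ratio 0.85 (Arm B rate 2.975), 80% power, two-sided 5%, 10% inflation. The window is 2 years. With a Poisson formula that takes the null variance at the control rate:

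n per arm = [1.960·√(2/3.5) + 0.842·√(1/3.5 + 1/2.975)]² / [(ln 0.85)²·2] = 87.1, so 88.

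88/0.9 = 97.8, so 98 per arm and 196 in total. The stated number reproduces. The difficulty lies in the outcome definition, not in the arithmetic.

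**2. Effect of non-attendance on the rate ratio.** Let pc and pt be the shares with no T-transfer in Arms A and B. Let h be their event rate relative to the average of their whole arm, with the same h in both arms. Excluding them multiplies the rate ratio by

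k = [(1 − pt·h)/(1 − pt)] / [(1 − pc·h)/(1 − pc)].

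The article gives neither pc, pt nor h. All values below are assumptions.

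| pc | pt | h | k | a true 0.85 reads | a true 1.00 reads |
|---|---|---|---|---|---|
| 10% | 10% | 1.5 | 1.00 | 0.85 | 1.00 |
| 5% | 3% | 1.5 | 1.01 | 0.86 | 1.01 |
| 15% | 5% | 0.5 | 0.94 | 0.80 | 0.94 |
| 15% | 5% | 1.5 | 1.07 | 0.91 | 1.07 |
| 15% | 5% | 2.0 | 1.15 | 0.98 | 1.15 |

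Example for 15% v 5%, h = 2: (0.90/0.95)/(0.70/0.85) = 0.947/0.824 = 1.15. Because h is relative to the whole arm, h = 2 means that control non-attenders have 2/0.824 = 2.4 times the rate of control attenders. That row is towards the extreme.

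**3. Effect on power when non-attendance is equal.** With the formula in step 1 and no other loss, if 10%, 20% or 30% of the 98 per arm never reach T-transfer, power is 80.5%, 75.9% or 70.4%. The 10% inflation covers the first case. It restores numbers, not comparability.

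**4. Alternative clocks, same formula, rate 3.5 throughout.**
- 24 months from a fixed date, with ratio 0.85 holding over that window: 88 per arm before inflation, 196 in total. N is unchanged.
- If 6 of those 24 months fall before transfer and carry no effect (assumption), the ratio becomes (6×1 + 18×0.85)/24 = 0.8875, and 88 evaluable patients per arm give about 55% power.
- From randomisation, with no pre-transfer effect (assumption): 1 year before transfer plus 2 after gives (1 + 2×0.85)/3 = 0.90 over 3 years, or 153 per arm (306 in total). Two years before plus 2 after gives 0.925 over 4 years, or 208 per arm (416).

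**The case against.** Several points stand on the other side.

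- **Attendance is not a stated target.** Table 1 lists self-care knowledge, pain and emotion management, and the relationship with oneself, others and care. It does not name attending the first adult consultation. A reader might infer that the programme sets out to change that event, but this is inference only. Both arms also receive the standard transfer steps, including a joint consultation and a visit to the adult department, which makes a large difference in attendance less likely. Nothing guarantees, however, that the visit takes place, or at the same time in both arms.
- **The 15% v 5% split has no source.** The article says only that missed appointments are common, which is not the same as never attending. Small or equal non-attendance leaves little or no bias.
- **The 4-year limit is mostly handled.** A patient included at 16.0 and first seen after 18.0 cannot complete 24 months, but the offset credits the time actually observed. Bias would need truncation to differ by arm and rates or effects to change over time. The article shows neither.
- **Leaving out pre-transfer events is defensible.** The Background states that "the highest morbidity and mortality is observed between 17 and 18 years of age", which might suggest that the window misses the worst period. The same sentence also reports frequent acute care after transition, which supports a post-transfer window, and the programme is still being delivered before transfer.
- **Unseen documents** may define analysis sets. The article also has a dropout rule and the 10% inflation, but these address numbers.

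None of this supplies a window for a patient without T-transfer. The outcome as fixed in the article requires the consultation.

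**Conclusion.** The point holds as a weakness in how the primary outcome is anchored. The window opens at an event after randomisation that the programme may influence. Patients without that event leave the primary comparison, so the analysed groups are post-randomisation subsets.

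A reader might go further and conclude that the randomised comparison is lost. The article does not support that, because the damage depends on how many patients never attend and on whether this differs by arm, and neither is given. The bias is nil with equal non-attendance and the same relative event rate in both arms. It is a factor of 0.94 to 1.15 under the assumed 15% v 5% with a relative rate of 0.5 to 2. The sign is unknown: the bias could hide a true 0.85 or produce an apparent benefit. Differences in the date of transfer, and so in age during the window, come on top and are not quantified here.

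**What to change.** 1. Pre-specify an analysis of all randomised patients over a 24-month window that starts, for everyone in both arms, at one date independent of attendance: for example the 18th birthday, or a fixed time after randomisation. Make it the primary analysis, or a key sensitivity analysis beside the post-transfer count. A fallback date for non-attenders alone would not be enough, since attenders would still start at a post-randomisation event. A window from the 18th birthday ends at age 20, which fits the 4-year limit even for a patient included at 16.0.
2. Add a supportive count of all events from randomisation, with log person-time as offset, and state that it has less power if there is no pre-transfer effect.
3. Report the proportion reaching T-transfer, and the time to it, by arm.

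**Cost.** The wording changes and two further models are small. N stays at 196 if 3.5 per year and 0.85 are kept for the new window. Pre-transfer time in the window may dilute the effect, as step 4 of the working shows, and this bears on whether the analysis is made primary or sensitivity. Records must be reviewed for non-attenders. Their admissions outside the index hospital may be missed and would count as zero. Because patients give their own written consent at 18, the plan should also say how that is obtained from those who do not attend.

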**Discussion:**

By providing self-care knowledge and coping skills related to SCD and therapeutics, helping empower patientsin relation to pain management and emotions, and facilitating the relationship to oneself, others, and care in Arm B of the DREPADO study, we believe that the morbidity and mortality of patients with SCD may be reduced after the proposed paediatric-adult transition programme.

**Trial registration:**

ClinicalTrials.gov, ID: NCT03786549; registered on 17 December 2018; https://clinicaltrials.gov/.

## Contributions to the literature

Sickle cell disease (SCD) is poorly represented in the literature on chronic diseases, in particular on the management of care.During the paediatric-adult transition, there is an increased risk of discontinuity of care and subsequent morbidity and mortality, so improvement is essential. Based on scientific evidence, the proposed paediatric-adult transition programme used a biopsychosocial approach to consider the patient and their family within the whole system.Using the methodology of randomised controlled trials, this protocol contributes to the construction of evidence on the paediatric-adult transition of patients with SCD.

## Background

Sickle cell disease (SCD) is a chronic, genetic disease, widespread both around the world and in France. After diagnosis, patients with SCD require medical follow-ups, which are essential to prevent complications. The most frequent complications are vaso-occlusive crises (VOC; which are painful), acute chest syndrome (ACS), and stroke. Thanks to advancements in medical care, a majority of SCD patients worldwide live beyond 18 years of age [1], and therefore, patients initially followed in paediatric departments are then transferred to adult departments.

For patients with chronic disease such as SCD, this paediatric-adult care transition is a period with an increased risk of discontinuity of care [2, 3]. During this period, adherence to medication is sub-optimal [1, 4] and the rate of missed clinical appointments is high [5]. Furthermore, the highest morbidity and mortality is observed between 17 and 18 years of age [6], and young adults frequently use acute care (emergency care and hospitalisations) after paediatric-adult transition [7].

During the paediatric-adult transition, the patient will have to manage new interlocutors and places of care, as well as a different organisation of this. An important aspect to improve the health status of patients is, therefore, to involve both paediatric and adult departments of care in the transition [3]. In addition, the patient will have to manage personal issues related to the period of adolescence [8]: a period of psychological upheaval and adaptation of family roles [9]. To assess the needs of patients with SCD during this transition period, a qualitative study was conducted in Lyon (France). Parents, as well as adolescent and adult patients with SCD, were individually interviewed about it. Results revealed individual and also family needs that concerned knowledge of the disease, coping skills, therapeutics, and psychosocial aspects [10].

To take into consideration all these aspects, an interesting approach is to regard the patient with a whole system approach, as presented in the biopsychosocial or social-ecological model [11]. Based on this approach, the Social-Ecological Model of Adolescent and Young Adult Readiness to Transition (SMART) proposes a conceptual framework that describes factors influencing paediatric-adult transition in SCD [12]. This includes bioclinical factors such as complications, psychological factors such as pain perception, and social factors such as scholar absenteeism [12]. Some of these factors may be modified and therefore these could become part of the patient’s coping skills [11, 12]. For instance, a coping skill for managing complications may be knowing when to go to the hospital based on a patient’s own pain threshold. For this, a pluridisciplinary team is required [12].

Currently, only pilot studies of transition programmes based on biopsychosocial approaches have been performed [13–16], with encouraging primary results [13].

The DREPADO open-label, individual, multicentre, randomised controlled trial (RCT) proposes to assess a paediatric-adult transition program for patients with SCD based on a biopsychosocial approach and SMART compared to standard care management. As compared to available studies that have investigated the paediatric-adult care transition [13], the originality of this study is the biopsychosocial approach coupled to its randomised controlled design. The purpose of the article is to present the DREPADO study protocol.

## Methods/Design

### The aim, design, and setting of the study

The DREPADO RCT seeks to assess the impact of a paediatric-adult transition programme. This trial is an interventional study. It is an open-label, individual, multicentre RCT comparing a control group (Arm A) to an interventional group with a paediatric-adult transition SCD programme based on the biopsychosocial approach (Arm B).

The DREPADO trial is a French national RCT including centres specialised in SCD patient care, involved in the SCD health network (*Maladie Chronique du Globule Rouge et des autres maladies de l’érythropoïèse* Filière - MCGRE) accredited by the French Ministry of Health and motivated to participate in this study. The coordinating centre is Lyon University Hospital, and five other centres will participate (Créteil, APHP Kremlin-Bicêtre, Martinique, APHP Necker, Pontoise).

The follow-up period is a maximum of 4 years for each patient. Outcomes is assessed at baseline (T-inclusion), at transfer date – which corresponds to the first consultation in the adult department of care (T-transfer), 12 months after transfer (T-12), and 24 months after transfer (T-24).

